## Background

Acupuncture therapy is widely used for the treatment of Bell’s palsy in China and throughout the world [1–4]; however, its effectiveness is still debatable because conclusions drawn from Cochrane reviews [5, 6] and meta-analyses [7, 8] do not support its clinical application, whereas clinical trials tend to prove its efficacy [9, 10]. Except for some defects in the protocol design and implementation, different manipulations among Chinese and foreign physicians, and the lack of powerful evidence of objective detection and assessment besides the neurological function scale, are very important reasons for the conflicting opinions.

The detectable pathological changes of peripheral facial paralysis (including Bell’s palsy) are facial nerve edema and bioelectric conduction disorders. The former can be detected and evaluated using magnetic resonance imaging (MRI) [11–15], the latter using more sensitive neural electrophysiological methods [16].

Treatments for Bell’s palsy should differ according to the stage of the disease [17], and the most important factor in treatment is not the kind of manipulation but when to initiate the intervention, with the goal being to start in the acute stage within 7 days of palsy onset [18–20]. Currently, electroacupuncture is widely used in the treatment of Bell’s palsy, although there is inadequate evidence-based support, especially for use in the acute stage. On the one hand, some clinical experiences have revealed that an early and appropriate electroacupuncture therapy shortens the disease course and improves the curative effect [9, 21]. On the other hand, there are beliefs that electroacupuncture stimulation is not appropriate for patients in the acute stage of Bell’s palsy and that it is more likely to aggravate facial nerve edema and bioelectric conduction disorders. Thus, the efficacy of electroacupuncture for treating Bell’s palsy starting from the acute stage is yet to be investigated.

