### Acute stage

Patients in groups A and B will receive acupuncture therapy at the Cuanzhu (BL2), Yangbai (GB14), Sizhukong (TE23), Qianzheng, Yingxiang (LI20), Quanliao (SI18), Dicang (ST4), Hegu (LI4), and Taichong (LR3) points. The acupuncture points are identified according to the method of point location issued by the World Health Organization (WHO). The acupuncture needles will be inserted straightly or obliquely with a depth of 10–30 mm to bring about the desired sensation of *deqi* (see Table 2), and the needles will be left in place for 20 minutes. The acupuncture therapy will be performed once every 2 days. Accordingly, patients in group A (electroacupuncture in the acute stage) will receive electroacupuncture therapy at the Yangbai (GB14)-Sizhukong (TE23), Quanliao (SI18)-Yingxiang (LI20), and Qianzheng-Dicang (ST4) points (2 Hz, density wave, 20 minutes) once every 2 days. Patients in group C will not receive acupuncture therapy.

**Table 2 Tab2:** Acupuncture points and needle insertion procedures

Acupuncture point	Direction	Depth (mm)
GB14 (yangbai, affected side)	Transversely toward geisoma	20–30
SJ23 (sizhukong, affected side)	Obliquely toward partes temporalis	20–30
Qianzheng (extra point, affected side)	Perpendicular to the skin	20–30
LI20 (yingxiang, affected side)	Obliquely along nasolabial sulcus toward the root of the nose	20–30
SI18 (quanliao, affected side)	Perpendicular to the skin	20–30
ST4 (dicang, affected side)	Transversely toward ST6	10–20
LI4 (hegu, bilateral)	Perpendicular to the skin	20–30
LR3 (taichong, bilateral)	Perpendicular to the skin	20–30

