### Stable and recovery stages

Patients in groups A–C will receive straight or oblique acupuncture with a depth of 10–30 mm at the Cuanzhu (BL2), Yangbai (GB14), Sizhukong (TE23), Qianzheng, Yingxiang (LI20), Quanliao (SI18), Dicang (ST4), Hegu (LI4), and Taichong (LR3) points (identified according to the method of point location issued by the WHO) to bring out the desired sensation of *deqi* from the eighth day after palsy onset. The needles will be retained for 20 minutes. The electroacupuncture will be performed once every 2 days. Accordingly, patients in groups A–C will receive electroacupuncture therapy at the Yangbai (GB14)-Sizhukong (TE23), Quanliao (SI18)-Yingxiang (LI20), and Qianzheng-Dicang (ST4) points (2 Hz, density wave, 20 minutes). All patients will be given therapies until the endpoint of complete recovery or study withdrawal.

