### Statistical analysis

In this study, statistical analyses of data will be performed by professionals rather than investigators using intention-to-treat and per-protocol approaches. All demographic and clinical characteristics of the subjects (such as sex, age) will be processed based on descriptive analyses. Quantitative data will be presented as average, standard deviation, median value, and range. Qualitative data will be presented as the frequency and percentage.

For the primary outcome measurements, a repeated-measures multifactorial analysis will be performed to identify differences between groups (differences within each group based on time, and the effects of the interaction of the variables based on group) to compare the differences in HB and Sunnybrook score changes between the interventional and control groups based on time (baseline, every treatment time and 1 month after palsy onset). The period from the onset to the first change in facial paralysis evaluation scale score in and the patients’ overall recovery period will be compared using one-way analysis of variance (ANOVA) between all groups. For the secondary outcome measurements, a χ^2^ test will be used to compare the edema onset frequency of the facial nerve on the affected side. One-way ANOVA will be applied to identify differences in results of facial nerve electromyography and F-wave detection between groups. In cases of non-normally distributed data, the Kruskal-Wallis H test will be performed.

All adverse events reported during the study will be included in the clinical report, and the prevalence of adverse events will then be calculated. The percentage of participants with adverse events in each group will be calculated and compared using the χ^2^ test or Fisher’s exact test. Statistical analyses will be performed using IBM SPSS for Windows version 19.0 statistical software (IBM, Armonk, NY, USA). All the tests will be two-sided, and a *P* value <0.05 will be considered statistically significant.

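### Adverse events are compared as one whole-study percentage per group, which dilutes the A, B, C contrast that exists only before day 8

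*Protocol article*

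**What the plan says.** The Statistical analysis section gives adverse events a short paragraph. Collection runs over the whole trial: "All adverse events reported during the study will be included in the clinical report". The summary and test are then fixed: "The percentage of participants with adverse events in each group will be calculated and compared using the χ^2^ test or Fisher’s exact test". Tests are two-sided at 0.05. No stage, onset window or cut at day 8 is mentioned, and the text does not say whether the test is pairwise or across all four groups.

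The treatment sections show where the groups differ:

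- **Acute stage:** "patients in group A (electroacupuncture in the acute stage) will receive electroacupuncture therapy at the Yangbai (GB14)-Sizhukong (TE23") and the other paired points every 2 days. Group B has manual acupuncture on the same schedule. For the third arm, "Patients in group C will not receive acupuncture therapy".
- **Stable and recovery stages, from the eighth day after onset:** "Accordingly, patients in groups A–C will receive electroacupuncture therapy at the Yangbai (GB14)-Sizhukong (TE23), Quanliao (SI18)-Yingxiang (LI20), and Qianzheng-Dicang (ST4) points", with the same settings and frequency.
- **Western medicine treatment:** every group takes the oral drugs, and group D is never needled.

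The Background reports this belief: "electroacupuncture stimulation is not appropriate for patients in the acute stage of Bell’s palsy and that it is more likely to aggravate facial nerve edema". Conduction disorder is named there too.

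**The concern.** The randomised difference between A, B and C lasts less than a week, while the adverse event count runs for the whole study. The count is also ever/never. A patient with an acute-stage event who has another event later contributes the same as a patient with only the later event. Any acute-stage excess in A is therefore partly masked by events that A, B and C share after day 8.

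What is at stake is how a null result is read. Starting electroacupuncture in the acute stage is the strategy under test, and the Background presents its suitability at that stage as disputed. A non-significant whole-study comparison could be taken as reassurance about early treatment when it had little chance of detecting an excess.

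**Working it through.** **Inputs from the article.** There are 33 patients per group (Sample size calculation) and tests are two-sided at 0.05 (Statistical analysis). Onset is within 2 days of entry (Inclusion criteria). Sessions are every 2 days, and shared treatment starts on day 8 (Acute stage; Stable and recovery stages). Table 1 gives 12 sessions, 3 per week for 4 weeks. The article states no adverse event rate and no power for this comparison, so there is no figure of the plan to reproduce. The 33 is used only as the group size.

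**Assumptions.** Event risks per session and background risks are assumed, with independence between sessions and between stages.

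**1. Dilution.** Let a and c be the acute-stage risks in A and C, and q the first-event risk from day 8, equal in both. Whole-study risks are 1−(1−a)(1−q) and 1−(1−c)(1−q). Their difference is (a−c)(1−q), so it shrinks but does not vanish unless q = 1.

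Example with assumed a = 30% and c = 5%, 33 per group:

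| q | A | C | Difference (points) | Power χ² | Power Fisher |
|---|---|---|---|---|---|
| 0 (acute stage only) | 30.0% | 5.0% | 25.0 | 0.78 | 0.70 |
| 10% | 37.0% | 14.5% | 22.5 | 0.55 | 0.45 |
| 30% | 51.0% | 33.5% | 17.5 | 0.30 | 0.25 |
| 50% | 65.0% | 52.5% | 12.5 | 0.18 | 0.14 |

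**2. Session counts.** Entry by day 2 and one session every 2 days gives 3–4 sessions up to day 7. Days 8, 10, …, 30 give 12 shared sessions, so A has 15–16 and C has 12. If Table 1's 12 sessions are instead the total in A, C has 12−3 = 9 or 12−4 = 8.

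**3. Per-session model.** With risk p per session and k sessions, the risk of any event is 1−(1−p)^k. At p = 5%:

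- Whole study, 15–16 vs 12 sessions: 1−0.95^15 = 54% or 1−0.95^16 = 56%, against 1−0.95^12 = 46%. Exact Fisher power is 7–10%.
- Whole study, 12 vs 9 or 8 sessions: 46% against 37% or 34%. Fisher power is 8–13%.
- Acute window, 3–4 vs 0 sessions: 14–18% against 0%. Fisher power is 33–59%.

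**4. Background events.** Every group takes the drugs, so 0% in C is optimistic. Add a background risk b during the acute stage, so that A has 1−(1−p)^k(1−b) and C has b. At p = 5% the acute-window Fisher power becomes:

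| b | Fisher power, 3–4 acute sessions |
|---|---|
| 0 | 33–59% |
| 5% | 24–40% |
| 10% | 19–31% |
| 20% | 12–18% |

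The same b leaves the whole-study comparison no better. Multiplying both event-free probabilities by (1−b) gives Fisher power of about 7–12% at b = 5% and 5–10% at b = 20%, over the session counts in step 3.

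**5. Other rates.** At p = 10%, whole-study Fisher power is 6–9% (15–16 vs 12 sessions) or 10–18% (12 vs 9 or 8). Acute-window power is 92–99% without background events and 58–78% with b = 10%. At p = 2%, both comparisons are weak.

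**6. A vs B.** A and B have the same number of sessions. If risk per session is equal for electrical and manual stimulation, the two groups do not differ in either window and the split gains nothing there. It helps only if the risks differ.

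**The case against.** A reader might infer that the whole-study table cannot show harm from acute-stage electroacupuncture. The article does not support that. A vs C remains a valid randomised comparison of adding acute-stage electroacupuncture, and a large excess could still appear: in the first table, χ² power is 0.55 when q is 10%.

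A reader might also infer that most events in A, B and C come from the shared phase. That depends on event rates the article does not give, and on few drug-related events early on.

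Nor does the plan rely on this table for the harm named in the Background. Edema and conduction are secondary outcomes, measured by MRI, electromyography and F waves within 7 days and at 1 month with their own tests. Clinical course is followed with the HB and Sunnybrook scales at each treatment and analysed over time. These objections stand. They leave a gap for other clinical adverse events, and the 1-month measurements also follow shared treatment.

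Finally, an article condenses, and a full protocol or SAP may tabulate events by stage. The text does not rule that out. The point is not a missing detail, however: the article names the summary and the test, and the comparison it names is poorly matched to arms that differ only before day 8.

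**Conclusion.** The point holds as a matter of sensitivity, not validity. The stated comparison pools the period in which A, B and C differ with a longer one in which they are treated alike, so a null result says little about clinical adverse events of acute-stage electroacupuncture. At an assumed 5% per session and 33 per group, A vs C has about 7–13% Fisher power over the whole study with no background events. The acute window gives 33–59% with none, 24–40% with 5% background and 12–18% with 20%. The advantage narrows as background risk rises and is absent at 2% per session. These sizes rest on assumed rates, session counts and independence; the (1−q) shrinkage needs only independence and an equal later risk. No primary conclusion of the trial changes. Minor severity, a cheap improvement.

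**What to change.** In the Statistical analysis section:

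1. Add a comparison of the percentage of participants with an adverse event whose onset falls between first treatment and just before the first day-8 session, A vs C and A vs B, with D shown alongside C. For C and D the window opens at the start of their medication. Name this as the comparison that addresses acute-stage safety.
2. Compare events with onset from day 8 on between A–C and D.
3. Keep the whole-study percentage per group as an overall summary, and say that it is not to be read as evidence on acute-stage safety.

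The cost is an onset date for each adverse event and revised wording. No extra patients or visits are needed and treatment is unchanged. Each window will hold fewer events, and with low event rates the acute-window comparison will still be imprecise.

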## Discussion

It is recognized that prednisolone but not antiviral medicine shows significant short- and long-term positive treatment effects in patients with Bell’s palsy [24–29]. This treatment should be used routinely for patients with Bell’s palsy and should be considered in all of these patients irrespective of degree of palsy [30]. It is noticed in clinics that acupuncture therapy alone is not likely to achieve significant curative effect without prednisolone for patients with HB scale scores equal to or over grade V. So, prednisolone is given to treat Bell’s palsy conventionally nowadays.

This study is designed based on a treatment including giving prednisolone, which will be used in every group. The purpose is to compare the different results of intervention by electroacupuncture, acupuncture, and non-acupuncture in the acute stage, followed by electroacupuncture in subsequent stages. Thus, the protocol is more likely to be in accord with current clinical practice and to be more conducive to protecting patients’ rights, as well as avoiding delay in treatment owing to bias of study design to a maximum extent. Hence, it is more scientific and reasonable to adopt a treatment strategy of Western medicine plus acupuncture therapy or electroacupuncture in the acute stage of Bell’s palsy facial paralysis.

The greatest uncertainty in this study is the effect of acupuncture or electroacupuncture on duration of disease or the completeness of ultimate recovery. However, either positive or negative effects eventually will be used to illustrate the facts, facilitating development of a reasonable clinical strategy in the future.

The aim of this study is to provide evidence of the effects of electroacupuncture therapy on Bell’s palsy. The sample size estimation of the present study was based on previous clinical scale evaluation, and the obtained sample size might, to some extent, differ from previous electrophysiological studies owing to the difficulty in obtaining data regarding the latter, such as mean values of a healthy population and patients with Bell’s palsy. This may be one of the aspects affecting the ultimate data analysis of the present study. Hence, it might be necessary to expand the sample size during the study to obtain credible results.

## Trial status

Recruitment started in January 2015 and will be completed by the end of May 2017.

## Abbreviations

ANOVA: Analysis of variance
ENoP: Neural electrophysiological
FOV: Field of view
HB: House-Brackmann
MRI: Magnetic resonance imaging
TR: Repetition time
TE: Echo time
WHO: World Health Organization
